### **3.3 Study procedures**

The planned overall study duration will be of approximately one hour per participant, and will include a recruitment period of thirty minutes and study duration of twenty minutes.

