### 2.2 Primary and secondary endpoints

In order to test the hypothesis, the primary endpoint will be whether or not the participants manage to maintain the optimized birthing position for the twenty minutes duration of the study, and if they do, how well they manage it. Some variables like age, parity or history of difficult delivery will be described for each participant. In complement to the primary endpoint, the number of parturients who will refuse to participate to the study will give additional insight into the acceptability of the optimized birthing position. If the reason of their refusal is mentioned, it will then be used to give an additional insight into the acceptability of the optimized birthing position.

The secondary endpoint variables will include:

- General information
- Risk factors of non-engagement of the foetus at full dilation
- Foetal parameters
- Delivery outcome

- Adverse events
- Presence of symphyseal separation

However, this study was not design to obtain significant results regarding the secondary endpoint variables.

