## **2.4 Study intervention**

The intervention will consist in positioning the parturient in an optimized position. It means the parturient will be asked to adopt a supine position with a hyperflexion of the thighs and a flat back, and to maintain the position for twenty minutes. This period of time represents approximately twenty uterine contractions and will give the opportunity to appreciate the effectiveness of the measure without being to constraining for the participants. Most of the time, the patients indeed have epidural anaesthesia and it is though not recommended to make them adopt a position for a prolonged amount of time, in order to avoid any risk of malposition or nerve compression. Help from the investigator or the midwife in charge will be provided if needed or requested. The labour will continue during the twenty minutes period, as obstetrical labour once started can't be interrupted.

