### **5.7 (Premature) termination of study**

The Project Leader may terminate the study prematurely according to certain circumstances, e.g.

- Ethical concerns,
- Insufficient participant recruitment,
- When the safety of the participants is doubtful or at risk (e.g. when the benefit-risk assessment is no longer positive), in particular if sensitive or motor nervous lesions occur.
- Alterations in accepted clinical practice that make the continuation of the study unwise, or
- Early evidence of harm or benefit of the experimental intervention

Upon regular study termination, the Ethics Committee is notified via BASEC within 90 days (ClinO, Art. 38).

Upon premature study termination or study interruption, the Ethics Committee is notified via BASEC within 15 days (ClinO, Art. 38).

All health-related data are anonymised upon end of data analysis.

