## **8 MONITORING AND REGISTRATION**

In this pilot study, the investigators will be attentive to the reporting of eventual adverse event during labor and in the following days. [name], doctor in the department of Gynaecology and Obstetrics of the CHUV, will perform the monitoring of the study. A peer protocol reviewed by the research team and [name] will be planned when the first five inclusions will be done. All the data will be accessible by the [name] and on demand by the CHUV institution.

Registration in French in the Swiss National Clinical trial Portal (SNCTP via BASEC) is planned. In addition, the study will be registered in the WHO International Clinical Trials Registry Platform (ICTRP; <http://www.who.int/ictpr/en/>).

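### The stated hour per participant does not cover the protocol's later endpoints, and nerve lesions, a named reason to stop the study, are sought after the position only through unscheduled reporting over an undefined period

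*Protocol*

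**What the plan says.** Section 3.3 is the whole of the study procedures. It gives the duration per participant ("The planned overall study duration will be of approximately one hour per participant") and its parts: it "will include a recruitment period of thirty minutes and study duration of twenty minutes". It schedules no assessment after the position.

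Other sections look beyond that hour:

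- Section 2.2 lists, among the secondary endpoint variables, "Delivery outcome", adverse events and "Presence of symphyseal separation", with no time or method of assessment.
- Section 2.4 says of the labouring women: "Most of the time, the patients indeed have epidural anaesthesia". It gives this as the reason for not holding a position long, "in order to avoid any risk of malposition or nerve compression".
- Section 5.7 lets the Project Leader stop the study when safety is in doubt, "in particular if sensitive or motor nervous lesions occur".
- Section 8 says that "the investigators will be attentive to the reporting of eventual adverse event during labor and in the following days". The number of days is not given.
- Section 5.2 requires serious events to reach the Project Leader within 24 hours, and has women with ongoing reported events followed, in hospital or at the polyclinic, until resolution or stabilisation.

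**The concern.** The protocol identifies a specific hazard of the intervention and makes it a particular reason to stop, but does not say when, how or by whom it is looked for once the 20 minutes are over. Section 3.3 offers no later contact, and section 8 relies on events being reported.

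What is at stake is the meaning of a negative result. In a study of about 20 women, a report of no nerve lesions and no symphyseal separations is only as informative as the share of women in whom these were actively ascertained. If that share is unknown, the count cannot support the safety of the position in later work, and the section 5.7 decision rests on whatever happens to be reported.

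**Working it through.** **1. The plan's own figure.** Section 3.3: 30 minutes recruitment + 20 minutes position = 50 minutes, which agrees with about one hour. The figure is not wrong in itself. Section 3.2 places information and written consent at an antenatal consultation before labour-ward admission, so the two parts are not continuous. The hour is best read as the time asked of the woman.

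**2. What the hour does and does not contain.**

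| Item | Where named | Within the 20 minutes? | Stated way of finding it later |
|---|---|---|---|
| Position maintained | 2.2, primary | Yes | Not needed |
| Delivery outcome | 2.2, secondary | Not necessarily | None stated |
| Symphyseal separation | 2.2, secondary | Not necessarily | No time or method stated |
| Adverse events | 2.2, secondary | In part | Attention to reports, days undefined (8) |
| Nerve lesions | 5.7, reason to stop | Not necessarily | Attention to reports, days undefined (8) |

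**3. Do other sections supply detection?** The 24-hour rule in section 5.2 moves a serious event to the Project Leader once it is known. The follow-up paragraph in the same section applies to events already reported. Both act after detection and neither produces it. Section 3.4 adds that a woman withdrawn, for example because labour progresses, contributes the data available. No safety assessment is fixed for her.

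**4. How much incomplete ascertainment could matter.** The protocol gives no lesion rate and no ascertainment share, so both are assumptions. With n women who start the position, lesion rate p and share s of lesions ascertained:

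P(at least one lesion seen) = 1 − (1 − p·s)^n

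For n = 20 (section 3.1), at p = 5%:

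- s = 1: 1 − 0.95^20 = 0.642
- s = 0.5: 1 − 0.975^20 = 0.397

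The full range for n = 20:

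| Assumed p | s = 1 | s = 0.5 | s = 0.2 |
|---|---|---|---|
| 1% | 18% | 10% | 4% |
| 5% | 64% | 40% | 18% |
| 10% | 88% | 64% | 33% |

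Section 1 gives fifteen to twenty women. For n = 15 the chances at 1%, 5% and 10% are 14%, 54% and 79% with s = 1, and 7%, 32% and 54% with s = 0.5.

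**5. The same point from a zero count.** With 0 of 20 and full ascertainment, the one-sided 95% upper limit for the lesion rate is 1 − 0.05^(1/20) = 13.9%. If only half of lesions are ascertained, this limit applies to p·s, so the limit for p is 13.9% / 0.5 = 27.8%. If s is unknown, no limit for p can be stated.

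**The case against.** The best defence is that section 3.3 gives a time burden, not a cut-off. Nothing there says that observation stops, and section 2.2 plainly intends data to be collected later. Section 8 extends attention to adverse events beyond labour, names a doctor of the department as monitor and plans a review after the first five inclusions. Section 5.2 carries serious events to the Project Leader and follows ongoing ones to resolution. Section 3.2 gives the study team access to medical records. The case report form is not shown, so its items cannot be called absent.

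Most of this stands, and it rules out several stronger readings that a reader might infer:

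- **That observation ends after an hour.** Sections 5.2 and 8 contradict this.
- **That the section 5.7 safeguard does not work.** It is discretionary, has no threshold, and information can reach the Project Leader through sections 5.2 and 8.
- **That an epidural hides a deficit during the hour, or that lesions appear late.** This is clinical inference. The protocol supports only frequent epidural use and a concern about nerve compression.
- **That the next woman would be enrolled before the previous one's lesion is known.** The protocol gives no accrual rate.

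The defence does not supply a detection step. Permission to read records is not a plan to extract a given item from each of them, and attention to reports does not ask every woman.

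**Conclusion.** The point holds in a limited form. The stated hour does not cover the protocol's own later endpoints. After the position, the one hazard singled out for termination is found only through unscheduled, report-driven surveillance over an undefined number of days. A zero count for nerve lesions would not distinguish none occurred from not asked.

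The size cannot be derived from the documents. Under the assumed rates, capturing half of lesions instead of all lowers the chance of seeing any among 20 women by about 8 percentage points at a 1% rate (18% to 10%) and by 24 points at 5% and at 10% (64% to 40%, 88% to 64%). The direction is the same throughout, but the true rate and the true share missed are unknown. The observation window and the way a named stopping concern is ascertained belong in the protocol, so this is not a detail left to a statistical analysis plan. It should be changed, but it does not show a failed safeguard.

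**What to change.** Reconcile sections 2.2, 3.3, 5.7 and 8:

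- In 3.3, say that the hour is the time asked of the woman, and state the safety observation window separately, with its end defined. It should not shorten the follow-up of ongoing events in section 5.2.
- For every woman who started the position, including those withdrawn under section 3.4, record yes or no for lower-limb sensory or motor deficit and for symphyseal separation, taken from the existing postnatal care record before discharge. Mark a silent record as not assessed, not as no.
- Pass the results to the Project Leader for the section 5.7 decision.
- Report them with all women who started the position as the denominator, and give the number not assessed.

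This assumes that a usable postnatal record exists, which the protocol does not describe; section 3.2 provides for access to records. The cost is two items on the case report form, a few sentences in the protocol, and slightly longer data collection per woman. The duration told to women at consent should agree with the revised wording.

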### **3.4 Withdrawal and discontinuation**

A participant will be withdrawn from the study in case of withdrawal of informed consent, disease progression, occurrence of foetus cardiac rhythm disorder or labour progression. When a withdrawal occurs, data available will be collected, anonymised, used and archived using the same method as completed data from another participant.

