## 2 STUDY OBJECTIVES AND DESIGN

### 2.1 Hypothesis and primary objective

The hypothesis is that the optimized birthing position, as described in the first chapter of this protocol, is an acceptable and feasible position. This means that the included parturients will be able to maintain the optimized birthing position for a certain amount of time without giving up or feeling uncomfortable achieving it. The primary objective of the study is thus to determine, by clinically testing the optimized position on a reduced sample of parturients, if it is well accepted by them with a satisfaction scale.

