### **4.2. Handling of missing data and drop-outs**

Dropouts will be replaced by recruitment of subsequent new subjects. The data of the participants dropping out from the study before the end of the twenty minutes period will be handled and archived the same as the remaining data. The number of drop-outs will indeed contribute to assess the acceptability of the position.

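### Early stops are pooled across causes, so a woman stopped because labour advanced can be counted against the position's acceptability

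*Protocol*

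**What the plan says.** - **Protocol 2.1** describes an acceptable and feasible position as one that women can "maintain the optimized birthing position for a certain amount of time without giving up or feeling uncomfortable achieving it".
- **Protocol 2.2** makes the primary endpoint "whether or not the participants manage to maintain the optimized birthing position for the twenty minutes duration of the study" and, among those who succeed, how well they do so. It also plans to use the reasons women give for refusing to take part.
- **Protocol 2.4** places the test within active labour: "The labour will continue during the twenty minutes period".
- **Protocol 3.4** lists the grounds for withdrawal as "withdrawal of informed consent, disease progression, occurrence of foetus cardiac rhythm disorder or labour progression". Data from withdrawn women are "used and archived using the same method as completed data from another participant".
- **Protocol 4.2** refers to "The data of the participants dropping out from the study before the end of the twenty minutes period", handles those data like the rest, and adds: "Dropouts will be replaced by recruitment of subsequent new subjects". It then gives drop-outs a role in the result: "The number of drop-outs will indeed contribute to assess the acceptability of the position".

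None of these sections divides early stops by cause.

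**The concern.** The withdrawal list in 3.4 mixes events with different meanings for the study question. A woman who asks to stop tells us something about acceptability. A foetal rhythm disorder is a safety event and says nothing about whether she found the position tolerable. Labour progression is closer to the hoped-for effect: section 1 presents such postures as a way to help the foetus descend through the pelvic inlet, and section 6.1 looks forward to resolving obstructed labour without medical intervention.

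If all of these enter one drop-out count, and that count is read as evidence on acceptability, the position looks less acceptable the more often labour moves forward. The other part of the primary endpoint does not help, because it is assessed only in women who complete the twenty minutes. A woman whose labour advanced at minute 15 therefore has no place there either.

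**Working it through.** The protocol states no rate, threshold, power or sample size calculation, so there is no figure to reproduce. The check has two parts: how the text scores a clinical stop, and an illustration with assumed counts.

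**1. Following one woman through the text.** Labour continues during the test (2.4), so progression inside the window is possible. If it occurs, she is withdrawn (3.4). She has then left before twenty minutes, which is the only feature by which 4.2 describes a drop-out, and the number of drop-outs informs acceptability. Under 2.2 she has not held the position for twenty minutes, and no third category exists. Under 2.1, however, she has neither given up nor necessarily felt uncomfortable. The scoring in 2.2 and 4.2 can therefore disagree with the construct in 2.1.

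**2. Effect on completion.** Section 1 gives fifteen to twenty women and section 3.1 gives twenty. Assume N = 20, of whom 2 give up by choice and k are stopped for labour progression or foetal rhythm disorder. Completion is (N − 2 − k)/N if everyone counts, and (N − 2 − k)/(N − k) if the k women are set aside. Intervals are exact (Clopper-Pearson) 95%.

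| k | All counted | Clinical stops set aside |
|---|---|---|
| 0 | 18/20 = 90% | 18/20 = 90% |
| 1 | 17/20 = 85% | 17/19 = 89% |
| 3 | 15/20 = 75% (51–91%) | 15/17 = 88% (64–99%) |
| 5 | 13/20 = 65% (41–85%) | 13/15 = 87% (60–98%) |

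Each clinical stop costs 1/20 = 5 points in the middle column and hardly moves the right-hand one. With N = 15 and k = 3 the two figures are 10/15 = 67% and 10/12 = 83%.

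**3. How likely is at least one such stop?** The chance per woman is an assumption, q. The probability of one or more among 20 is 1 − (1 − q)^20, which gives 64%, 88%, 99% and over 99% for q = 5%, 10%, 20% and 30%.

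**4. Which denominator for acceptability?** Suppose 80% would tolerate twenty minutes and 40% are interrupted clinically (both assumed, and independent of each other).

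- *Interruption always comes first.* Stops by choice are 0.20 × 0.60 = 12% of all who started. That implies 88% acceptance against a true 80%. Excluding interrupted women gives 0.12/0.60 = 20% stopping, which is correct.
- *Giving up always comes first.* Stops by choice are 20% of all who started, which is correct. Completers are 0.80 × 0.60 = 48%, so excluding interrupted women gives 0.20/(0.20 + 0.48) = 29%, which is too high.

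Neither denominator is right in every case. Over all who started, acceptance tends to be overstated. Both should be shown, with minutes held.

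**The case against.** The strongest reply is that the protocol never states this misclassification outright. Section 3.4 speaks of women being withdrawn and 4.2 of women dropping out, and no sentence equates the two or says that a drop-out counts against the position. A reader might infer that every withdrawal under 3.4 is by rule a failure of acceptability, but the text does not go that far. What stands is that 4.2 describes drop-outs by time alone and 2.2 has only two outcomes, so the pooled count is a natural result of following the wording.

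Three further inferences are tempting and not supported:

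- **That replacement removes from the sample the women whose labour progressed.** Sections 3.4 and 4.2 both keep and use their data, so replacement adds women and takes none away. What is left open is whether replaced women stay in the denominator.
- **That completion is a biased measure as such.** Section 2.1 asks about feasibility as well as acceptability, and holding the position for twenty minutes whatever the reason for stopping is a legitimate feasibility measure. The problem arises only when it is read as acceptance.
- **That a definite bias can be quoted.** Any range depends wholly on assumed interruption rates.

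It is also fair to say that handling by reason could appear in an analysis plan or CRF not shown here. That does not remove the point, because the protocol itself fixes the two-way endpoint and gives the undivided drop-out count a role in judging acceptability. It plans to use reasons for refusal but says nothing equivalent for early stops.

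**Conclusion.** The concern holds as a matter of definition. Sections 2.2, 3.4 and 4.2 together allow labour progression, the effect the position is meant to promote, to be counted as evidence against its acceptability, contrary to the meaning given in 2.1. The argument rests mainly on labour progression. Foetal rhythm disorder is not a favourable outcome, but it is not the woman's refusal either.

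The size cannot be derived from the protocol. The 5 points per clinical stop assumes 20 women and that every such stop is scored as not completed. The study is a qualitative pilot with no acceptability threshold, and drop-outs only contribute to the judgement beside the satisfaction scale and refusals, so no stated decision rule would be tripped. It is a moderate correction, best made before enrolment, because a reason not recorded at the bedside may not be recoverable later.

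**What to change.** In 2.2, 3.4 and 4.2:

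1. Record the time and reason of each stop before twenty minutes as (a) the woman's own decision or discomfort with the position, (b) labour progression or delivery, or (c) foetal rhythm disorder or another medical reason.
2. State that only (a) counts as non-acceptance.
3. Report the proportion who held the position for twenty minutes over all who started, replaced women included, as feasibility.
4. For acceptability, report the counts of (a), (b) and (c) with minutes held. Give the proportion stopping for (a) twice: over all who started, and with (b) and (c) excluded or censored at the time of stop. Note that the first tends to overstate acceptance.

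The cost is one CRF item and a few sentences. No extra participants are needed, and the clinical rules for stopping are not touched.

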## **4 STATISTICS AND METHODOLOGY**

### **4.1. Statistical analysis plan and sample size calculation**

In this observational pilot study, no sample size was defined.

### **4.2. Handling of missing data and drop-outs**

Dropouts will be replaced by recruitment of subsequent new subjects. The data of the participants dropping out from the study before the end of the twenty minutes period will be handled and archived the same as the remaining data. The number of drop-outs will indeed contribute to assess the acceptability of the position.

## 5 REGULATORY ASPECTS AND SAFETY

### 5.1 Local regulations / Declaration of Helsinki

This study is conducted in compliance with the protocol, the current version of the Declaration of Helsinki, the ICH-GCP, the HRA as well as other locally relevant legal and regulatory requirements.

### 5.2 (Serious) Adverse Events

An Adverse Event (AE) is any untoward medical occurrence in a patient or a clinical investigation subject which does not necessarily have a causal relationship with the trial procedure. An AE can therefore be any unfavourable or unintended finding, symptom, or disease temporally associated with a trial procedure, whether or not related to it.

A Serious Adverse Event (SAE) (ClinO, Art. 63) is any untoward medical occurrence that

- Results in death or is life-threatening,
- Requires in-patient hospitalisation or prolongation of existing hospitalisation,
- Results in persistent or significant disability or incapacity, or
- Causes a congenital anomaly or birth defect

The Project Leader makes a causality assessment of the event to the trial intervention, (see table below based on the terms given in ICH E2A guidelines). Any event assessed as possibly, probably or definitely related is classified as related to the trial intervention.

| Relationship                                                                            | Description                                                                                                               |
|-----------------------------------------------------------------------------------------|---------------------------------------------------------------------------------------------------------------------------|
| Definitely                                                                              | Temporal relationship
Improvement after dechallenge*
Recurrence after rechallenge
(or other proof of drug cause) |
| Probably                                                                                | Temporal relationship
Improvement after dechallenge
No other cause evident                                          |
| Possibly                                                                                | Temporal relationship
Other cause possible                                                                             |
| Unlikely                                                                                | Any assessable reaction that does not fulfil the above conditions                                                         |
| Not related                                                                             | Causal relationship can be ruled out                                                                                      |
| *Improvement after dechallenge only taken into consideration, if applicable to reaction |                                                                                                                           |

The Project Leader makes a severity assessment of the event as mild, moderate or severe. Mild means the complication is tolerable, moderate means it interferes with daily activities and severe means it renders daily activities impossible.

